**Methods and analysis:**

This prospective cohort study, as part of a PhD project, will be carried out on 200 elite handball players of first men's handball league in Slovenia during an entire handball season, lasting from July 2022 to June 2023. Primary outcomes, including health problems, loads and stress, will be assessed weekly on a player level. Other player-related outcomes will include anthropometry, life event survey and blood biomarkers (cortisol, free testosterone and Ig-A), which will be taken three to five times across the observation period according to the players’ training cycle.

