## Methods and analysis

### Study design

The study is designed as a prospective cohort study. All measurements will be conducted over a single handball season, lasting from July 2022 to June 2023 (a total of 46 weeks), with weekly reporting (table 1) and three to five biomarker sampling timepoints (figure 1). We used the Standard Protocol Items: Recommendations for Interventional Trials (SPIRIT) checklist when writing our report.^37^

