### Participants and sample size

A power analysis was a priory determined using the G*Power software.^38^ Based on previous studies with similar design, we expected to find nearly two times as high odds of injury occurrence in athletes during a period of high academic stress compared with low academic stress (OR=1.78; effect size (ES)=0.14)^25^ with power of 0.90 and α=0.05, two-tailed, which calculated an initial sample size of 134 participants. As in sports practice, the athlete drop-out is to be expected (due to travelling, international transfer to another club/state, etc); we adjusted the originally calculated sample size by following formula: N1=n/(1−d),^39^ where N1 is adjusted sample size, n is the sample size required as per the proposed formula (N=134) and d is the drop-out rate (d=0.10). This resulted in total sample size of 149 athletes. Inclusion criteria will be as follows: DC and non-DC registered male handball players who are competing in the first Slovenian handball league and are above 18 years of age.

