### Statistical analysis

Statistical analysis will be performed using standard statistical software (SPSS V.27.0, IBM, Armonk, New York). Descriptive statistics will be used for all variables. Normality of data distribution will be assessed using the Shapiro-Wilk test. In case of non-normally distributed data, non-parametric statistics will be used, otherwise, the statistics for normally distributed data will be used. The data will be analysed using a logistic regression model to properly account for the dependency induced by the repeated observations over time within each subject. Main effect of all dependent variables on injury/illness occurrence will be studied using repeated measures analysis of variance (ANOVA) with time (preparation period vs competition period vs off-season period) as within factor, while group (injured/ill vs healthy) as between factor. Where significant effects will be found for group, time effects or two-way interactions, pairwise comparisons will be used to address the significant differences for each variable independently. For comparison of the groups, we will use independent t-test. The magnitude of effect for all dependent variables will be reported as partial eta squared (η^2^). In addition, *Cohens’ d* (ES) will be used to assess magnitude of difference between groups. Furthermore, regression analysis will be used to assess predictive power of individual parameters to identify injury/illness occurrence. For the correlation of subjective measures of stress with the objective measures, bivariate correlation will be used. Additionally, Bland-Altmann analysis will be used (low/high stress normative values) as previously recommended.^42^ Furthermore, receiver operating characteristic (ROC) curve analysis will be used for defining the cut-off values. Hypotheses will be accepted or rejected at p≤0.05.

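### The injured/ill versus healthy t-tests ignore weeks observed and can be biased by drop-out; load inference should rest on the player-week model

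*Protocol article*

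**What the plan says.** All references are to the protocol article.

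- **Study design** sets the observation period: "lasting from July 2022 to June 2023 (a total of 46 weeks". The abstract gives the frequency: "Primary outcomes, including health problems, loads and stress, will be assessed weekly on a player level".
- **Participants and sample size** anticipates losses: "athlete drop-out is to be expected (due to travelling, international transfer to another club/state, etc". The drop-out rate is set at 0.10, which raises the target from 134 to 149.
- **Statistical analysis** names three analyses that matter here:
  - a "logistic regression model to properly account for the dependency induced by the repeated observations over time within each subject";
  - a repeated-measures ANOVA with "time (preparation period vs competition period vs off-season period) as within factor" and "group (injured/ill vs healthy) as between factor";
  - the group test, "For comparison of the groups, we will use independent t-test", with Cohen's d for the size of the difference.

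ROC analysis is to supply cut-off values. The section does not say which analysis carries the primary aim, over what window a player must be event-free to count as healthy, or whether load enters the t-test as a weekly mean or as a sum.

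**The concern.** To be labelled injured/ill, a player must have an event while under observation, so the label depends partly on how long he was watched. A player who transfers out in week 12 without an event and one who is event-free for all 46 weeks would both be healthy, and neither the t-test nor Cohen's d distinguishes them.

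Anything related to length of observation can then differ between the groups although it has no effect on injury or illness. Load summed over observed weeks is one such variable. Average weekly load is another, if players who leave train, play, study or work more or less than those who stay. The primary aim is to learn how load affects injury and illness, so a load difference that partly reflects follow-up time would be misread. ROC cut-offs would share the problem if they were built on the same two groups.

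**Working it through.** **The plan's own figure.** 134/(1 − 0.10) = 148.9, which rounds up to 149. The drop-out inflation is reproduced, and 149 players with 10% leaving are used below.

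**Assumptions not in the documents.** A constant weekly risk h of a first event, varied from 1% to 5%. Leavers go at a uniformly random week. Load has no true effect.

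**Step 1: the label depends on follow-up.** P(labelled injured/ill after w weeks) = 1 − (1 − h)^w.

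| h | w = 12 | w = 46 |
|---|---|---|
| 1% | 1 − 0.99^12 = 11% | 1 − 0.99^46 = 37% |
| 2% | 1 − 0.98^12 = 22% | 1 − 0.98^46 = 61% |
| 4% | 1 − 0.96^12 = 39% | 1 − 0.96^46 = 85% |

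**Step 2: share of leavers among the healthy, if leavers are kept.** Averaged over w = 1 to 46, a leaver is labelled injured/ill with probability 20%, 36% or 56%. With 10% leaving, the share of leavers in the healthy group is 0.1 × P(leaver healthy) / [0.1 × P(leaver healthy) + 0.9 × P(stayer healthy)]:

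- h = 1%: 0.1 × 0.797 / (0.1 × 0.797 + 0.9 × 0.630) = 12%
- h = 2%: 0.1 × 0.645 / (0.1 × 0.645 + 0.9 × 0.395) = 15%
- h = 4%: 0.1 × 0.442 / (0.1 × 0.442 + 0.9 × 0.153) = 24%

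The corresponding share in the injured/ill group is 6 to 7%.

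**Step 3: does this produce a false load effect?** Simulation with no true load effect: 149 players, 10% leaving, weekly load mean 15 h and SD 3 h (assumed), 2,000 runs per cell, nominal level 5%. Type I error:

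| Load entered in the t-test | h = 1% | h = 2% | h = 5% |
|---|---|---|---|
| Weekly mean, leaving unrelated to load | 0.060 | 0.060 | 0.057 |
| Weekly mean, leavers 1 SD lower | 0.066 | 0.088 | 0.164 |
| Sum over observed weeks | 0.142 | 0.348 | 0.709 |
| Player-week test, range over the three scenarios | 0.046–0.055 | 0.046–0.058 | 0.052–0.056 |

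The Monte Carlo standard error near 5% is √(0.05 × 0.95/2000) = 0.005, so the first row is compatible with 5%; the mean group difference there is at most 0.006 SD. For leavers 1 SD lower in load, the error over h = 1% to 4% is about 6 to 14%. In the same case, dropping the leavers brings it back to about 5%, at the price of their observed weeks.

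**The case against.** The strongest reply is that the section already plans a logistic regression for repeated observations. Outcomes and loads are weekly, and if that model is fitted on player-weeks each player contributes only the weeks in which he was seen. This stands: the weakness lies in the group comparisons, not in the whole analysis. It does not settle the matter, because the section assigns the main effects on injury/illness occurrence to the ANOVA with the injured/ill grouping, takes its effect sizes from the group comparisons, and ranks none of the analyses as primary.

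Second, nothing says that leavers are kept as healthy. The drop-out inflation treats them as lost, an ordinary repeated-measures ANOVA would usually omit a player with no off-season value, and the t-test can be read as a follow-up test within each period. This also stands. If leavers are dropped, the bias described here does not arise, but the weeks they reported are discarded.

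Third, a condensed article may leave group definitions and load aggregation to a fuller plan. That is fair, and their absence is not the point. The point is that a t-test without follow-up time is the named method, alongside an expected 10% drop-out.

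A reader might infer more: that the healthy group is mostly early leavers, or that follow-up time is bound to appear as a load effect. The documents do not support either. Leavers make up 12 to 24% of the healthy group at h = 1% to 4%, and at 4% about 56% of leavers are labelled injured/ill. Error rates of 14% and above at h = 1% to 4% need season-total load, which no section plans; loads are listed and reported per week, and sleep, perceived stress and the biomarkers do not accumulate.

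**Conclusion.** The concern holds in a limited form. The t-test and Cohen's d take no account of weeks observed, and a player followed for less time is more likely to be labelled healthy than a full-season player. Whether that biases a load comparison depends on choices and facts that the article does not give:

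- weekly means and leaving unrelated to load: no bias;
- leavers dropped: this bias is avoided, with loss of their data;
- leavers kept and 1 SD lower in load: type I error about 6 to 14% at weekly onset of 1 to 4%;
- load summed over observed weeks: larger inflation, but this analysis is not stated in the plan.

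The onset rates, the 1 SD difference and the uniform leaving times are all assumptions. The planned logistic regression is not affected if its unit is the player-week. The change is worth making because it holds up whichever way leavers would have been handled, and the weekly data it needs are already collected.

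**What to change.** In the Statistical analysis section:

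1. State that inference on load and injury/illness rests on the repeated-observation logistic regression fitted on player-weeks, or on a time-to-first-event model. Each player contributes only observed, at-risk weeks up to the date of leaving.
2. Take load from weeks before the event week. A mean over a player's whole follow-up would mix load before and after an injury, and reduced training after injury would contaminate the exposure.
3. Derive the ROC cut-offs on player-weeks in the same way.
4. Keep the injured/ill versus healthy t-test and Cohen's d as descriptive only.

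The cost is analysis wording and a derived record of each player's observed weeks, both available from the weekly reports. The downside is that the main effect measure becomes an odds or hazard ratio instead of Cohen's d.

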### Health monitoring and load management

One potential strategy for injury and illness prevention in elite sports is monitoring of external and internal loads. Monitoring an athlete’s workload has a number of potential benefits, including interpreting performance changes, increasing understanding of exercise responses, detecting fatigue and monitoring recovery needs, optimisation of the training programme and competition calendar. It also serves for providing adequate workload levels to reduce the risk of injury and illness^29 30^ and guide rehabilitation programmes. External and internal loads can be assessed with subjective and objective measures. External load measurement typically involves quantifying an athlete’s training or competition loads by reporting training hours, running length, amount of weight lifted, number of games played and other external factors such as life events, everyday problems and/or travel. On the other hand, internal load is measured by assessing the internal biological, physiological and psychological response to an external load^31^ such as heart rate or ratings of perceived exertion. A recent systematic review of internal stress monitoring has identified subjective reporting to be more sensitive and consistent than objective measurements in determining acute and chronic changes in an athlete’s well-being.^32^

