### Biomarkers

Biomarker discovery and validation is a critical aim of the medical and scientific community.^33^ Biomarkers can be used as an objective assessment tool for health, performance, recovery and talent identification in elite sport. Among the most critical hormones for athletes seem to be cortisol, testosterone, dehydroepiandrosterone and immunoglobulin-A (Ig-A). However, testosterone to cortisol (T:C) ratio is considered to be more sensitive to training stress than either measure alone,^33^ as several studies report poor performance outcomes and suboptimal training adaptations in athletes with a low T:C ratio.^34 35^ However, to the best of the authors’ knowledge, no previous work has examined the use of biomarkers for injury prevention, recovery after an injury or identification of individuals at increased risk.

Given all of the above, there is a need for better health surveillance, load monitoring and support services with an emphasis on injury/illness prevention and rehabilitation.^36^ As DC athletes have a wider variety of loads that pose greater psychophysiological strain to them, they could also be at an increased risk for injury/illness. Therefore, more comprehensive monitoring of potential risk factors in this specific population is warranted. It is not yet known, but important to determine how much of overall load can an athlete withstand before injury/illness occurs. Thus, the primary aim of this study is to determine how specific physical, psychosocial and DC loads affect the occurrence of injuries and illnesses in elite handball players and how much of a variation in the athlete’s load leads to an occurrence of an injury/illness. A secondary aim is to determine the association between objective and subjective measures of stress as well as examine the benefits of certain biomarkers to monitor stress, load and injury/illness occurrence in athletes.

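### For predicting injury and illness, no stated analysis asks whether the blood biomarkers add anything to the weekly questionnaire

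*Protocol article*

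**What the plan says.** The aims paragraph at the end of the Introduction (under Biomarkers) sets out to "examine the benefits of certain biomarkers to monitor stress, load and injury/illness occurrence in athletes". No comparator is named, and no criterion for a benefit.

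The Statistical analysis section contains these steps that bear on the biomarkers:

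- Repeated measures ANOVA and t-tests of injured/ill against healthy players, after which "pairwise comparisons will be used to address the significant differences for each variable independently".
- For prediction: "regression analysis will be used to assess predictive power of individual parameters to identify injury/illness occurrence".
- For the link with reported stress: "For the correlation of subjective measures of stress with the objective measures, bivariate correlation will be used", with a Bland-Altman analysis in addition.
- For thresholds: "receiver operating characteristic (ROC) curve analysis will be used for defining the cut-off values".
- A general logistic model: "The data will be analysed using a logistic regression model to properly account for the dependency induced by the repeated observations". Its covariates are not listed.
- A general decision rule: "Hypotheses will be accepted or rejected at p≤0.05".

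Under Weekly load and stress questionnaire, players report perceived stress (1–10), sleep, academic and work load every week, and teams report training and match load. Under Blood biomarkers, sampling takes place at three to five timepoints, within a season of 46 weeks (Study design).

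**The concern.** The questionnaire is collected from every player every week and needs no blood sample. For anticipating injury or illness, the practical question about a blood marker is therefore what it tells the team that the questionnaire does not. A marker's own association with the outcome does not answer that. The study also looks for markers that correlate with perceived stress. If stress is related to injury or illness, a marker that correlates with stress will be related to them too, even if it carries no further information.

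At stake is how the injury/illness part of the biomarker aim will be read. The abstract promises input to injury prevention strategies and policy, and the strengths and limitations box speaks of periodic athlete monitoring. A single-marker association could be taken as support for repeated blood sampling when the weekly question already carries the same information.

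**Working it through.** **1. The plan's own figure.** The only sample size calculation gives 134 players, inflated for 10% drop-out: 134 / (1 − 0.10) = 148.9, rounded up to 149. This reproduces. It rests on an odds ratio of 1.78 for injury in high against low academic stress. No figure is given for biomarkers or for added value, so the size of the problem can only be illustrated.

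**2. The stated steps against the question.**

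| Stated step | What it answers | Value beyond the questionnaire? |
|---|---|---|
| ANOVA, t-tests, pairwise follow-up | Does each variable differ between groups or periods? | No |
| Regression, individual parameters | Does each parameter predict? Univariable or joint not stated | Not stated |
| Bivariate correlation, Bland-Altman | Does the marker track or agree with reported stress? | No |
| ROC | Where to put a cut-off | No comparison of models stated |
| Logistic model for repeated observations | Covariates not listed | Not stated |

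No step compares a model holding questionnaire data with the same model plus biomarkers.

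**3. Illustration, if parameters are entered one at a time.** Assumptions, none of them given in the documents for this purpose: one observation per player; 50% with the outcome; standardised reported stress S with odds ratio 1.78 per SD (the protocol's odds ratio, carried over to a per-SD scale); a biomarker M = r·S + √(1 − r²)·noise, so that it has no effect of its own. Two logistic models were fitted, M alone and M with S, with 2,000 simulated studies per setting and p≤0.05.

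| Correlation r of M with S | M alone, N=149 | M alone, N=200 | M with S in the model, N=149 | Mean AUC of M alone, N=149 |
|---|---|---|---|---|
| 0 | 5% | 4% | 4% | 0.50 |
| 0.1 | 6% | 6% | 5% | 0.51 |
| 0.3 | 16% | 19% | 5% | 0.55 |
| 0.5 | 37% | 47% | 5% | 0.58 |
| 0.7 | 64% | 76% | 4% | 0.61 |

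N=149 is the calculated sample size; N=200 is the cohort named in the abstract.

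**4. Check by hand.** The slope of M alone is roughly r × ln(1.78) = 0.577r. Its standard error is roughly 1/√(149 × 0.25) = 0.164. The expected z is therefore about 3.52r: 0.35 at r=0.1, 1.06 at r=0.3 and 1.76 at r=0.5. The chance that |z| exceeds 1.96 is then about 6%, 18% and 42%. This is slightly above the simulated 6%, 16% and 37%, as expected, because the approximation ignores the shrinkage of a logistic slope when S is left out.

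**5. A second set of assumptions.** Let stress differ by d = 0.3 to 0.5 SD between cases and non-cases, with r = 0.3 to 0.5. The marker then differs by d × r = 0.09 to 0.25 SD, and its AUC is Φ(dr/√2) = 0.53 to 0.57. With 75 against 74 independent records, z = dr/√(1/75 + 1/74) = 0.55 to 1.53, which gives significance in about 9% to 33% of studies. The direction and order of size are the same.

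**The case against.** The strongest reply is that the protocol never says the parameters are tested one at a time. A reader might infer that, but a regression can report the contribution of single terms within a joint model, and a logistic model with unlisted covariates is announced as well. Covariate lists often sit in a full protocol or analysis plan that is not shown. This stands: it rules out saying that the plan uses univariable tests. It does not supply the missing comparison, since no stated step sets the questionnaire alone against the questionnaire plus biomarkers.

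A reader might also infer that a biomarker will be declared useful on p≤0.05. The article has no such rule; the threshold is a general one for hypotheses. Effect sizes, ROC curves and the correlation with stress would also be reported, and an AUC of 0.53 to 0.58 would look weak. That stands too. The correlation would reveal that a marker tracks stress, but not whether it predicts beyond stress.

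The aim is also wider than prediction. For monitoring stress, agreement with reported stress is a result the study is looking for, so it would be wrong to say that the secondary aim as a whole goes unanswered.

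Finally, the Introduction cites a review finding "subjective reporting to be more sensitive and consistent than objective measurements". It is tempting to read this as the protocol conceding that the questionnaire is the better predictor of injury. The sentence concerns changes in well-being and does not support that. The case for the questionnaire as comparator rests on its being collected weekly anyway.

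The illustrated percentages depend on assumed correlations and are close to nominal at r = 0.1. An association of M alone is also not a false positive in the strict sense: the marker does predict, but only through what the questionnaire already records.

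**Conclusion.** The point holds for the injury/illness part of the biomarker aim. The stated analyses cover single parameters, pairwise correlations and cut-offs, and none assesses what biomarkers add to the weekly questionnaire. If the regression is run one parameter at a time, a marker that only tracks perceived stress reaches p≤0.05 in about 6% (r=0.1), 16% (r=0.3) or 37% (r=0.5) of studies with 149 players, against 4–5% with reported stress in the model. These figures assume one observation per player, a 50% outcome rate and an odds ratio of 1.78 per SD of stress. They show the mechanism and are not a forecast for this study. If a joint model with the questionnaire items is already intended, the remaining defect is that the article does not say so.

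**What to change.** Keep the planned single-parameter and correlation analyses, and add one nested comparison for the injury/illness part of the aim:

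- **Outcome:** new injury or illness in a fixed window after each blood sample.
- **Base model:** perceived stress, sleep, training, match, academic and work load, as reported before that window opens. Same-week items should not be used. The health questionnaire and the load items cover the same 7 days, so lower load or higher stress may be a consequence of the injury or illness.
- **Extended model:** the base model plus the biomarkers.
- **Criterion:** a joint test of the added terms that respects repeated observations within player (for example a GEE Wald test or a mixed-model likelihood-ratio test; an ordinary likelihood-ratio test would ignore the dependence), and the change in AUC with a confidence interval from a bootstrap that resamples players.
- **Claim:** predictive benefit beyond the questionnaire is claimed only on this comparison. Agreement with reported stress is reported as a result for the stress-monitoring part.

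The cost is some extra analysis on data already collected. Only weeks near the blood samples contribute: with 149 players and complete sampling, 149 × 3 = 447 to 149 × 5 = 745 player-samples, so precision is limited. The biomarkers may also show less apparent value than they would alone.

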#### Life Events Survey for Collegiate Athletes Questionnaire

At the baseline and final measurements, the athletes will be asked to complete Life Events Survey for Collegiate Athletes (LESCA)^41^ in order to get more contextualised view of the life events that were happening in the past 12 months. LESCA is a 69-item questionnaire where athletes rate how each life event affected their lives in the past 12 months on a −4 to 4-point scale (−4, extremely negative to +4, extremely positive). The events include personal, academic-related and sports-related events. From summing the rated life events, two life stress scores, negative (NEG) and positive (POS) are obtained, while a total life stress score can as well be obtained by summing the NEG and POS scores together.^41^

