#### Weekly load and stress questionnaire

The teams will weekly report training and competition load for each athlete, while academic (educational activities, including lectures, exams and studying) and work load (a part-time or full-time job besides playing sports) for the past 7 days will be reported by the athletes themselves. Competition load will be reported in minutes for each game played in the past week, while training, academic and workload will be reported in hours. The athletes will additionally report average hours slept per day over the past week and rate their perceived overall stress of that week on the scale 1–10.

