#### Blood biomarkers

There will be three to five measurement timepoints for biomarker sampling, according to the training (preparatory period, competitive period, off-season period) cycle. The athletes will be tested under similar conditions every time, after a rest day (refrainment from intensive training the day before blood collection), between 7:00 and 10:00 in the morning.

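### The planned bivariate correlation of stress with biomarkers makes no provision for three to five pairs per player and, however it is run, does not isolate the within-player association that monitoring needs

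*Protocol article*

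**What the plan says.** All references are to the protocol article.

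- **Aim (Introduction, Biomarkers).** The secondary aim has two clauses. The first is general: "A secondary aim is to determine the association between objective and subjective measures of stress". The second is to "examine the benefits of certain biomarkers to monitor stress, load and injury/illness occurrence in athletes". Table 1 likewise lists monitoring as the purpose of the blood markers.
- **Data.** For the objective side, "There will be three to five measurement timepoints for biomarker sampling", spread over the preparatory, competitive and off-season periods. For the subjective side, players each week "rate their perceived overall stress of that week on the scale 1–10". A second subjective measure is taken only twice: "At the baseline and final measurements, the athletes will be asked to complete Life Events Survey for Collegiate Athletes".
- **Method (Statistical analysis).** "For the correlation of subjective measures of stress with the objective measures, bivariate correlation will be used". A Bland-Altman analysis is added. The decision rule is "Hypotheses will be accepted or rejected at p≤0.05".
- **Dependence.** The only sentence on repeated observations concerns a "logistic regression model to properly account for the dependency induced by the repeated observations over time within each subject". That model is for injury or illness occurrence, not for a correlation of two measured quantities.

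**The concern.** A simple Pearson or Spearman correlation assumes one independent pair per unit. If each blood sample is matched to a weekly stress rating, a player contributes three to five pairs.

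Two different questions can be asked of such data. Do players who report more stress have different biomarker levels (between players)? Does a player's biomarker move when his own stress moves (within player)? Using a marker to monitor stress depends on the second.

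If all player-timepoints go into one coefficient, the p-value can be too small and the coefficient blends the two associations. Any seasonal shift common to both variables enters as well. If the correlation is run one timepoint at a time, or on player means, the p-value is sound but within-player change is never examined.

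**Working it through.** **Inputs.** Samples per player k = 3 to 5 (Blood biomarkers). Threshold 0.05 (Statistical analysis). The plan gives no figure for the correlation itself. The player count used below is the plan's own: 134/(1 − 0.10) = 148.9, rounded up to 149, which reproduces the stated sample size. The ICCs of stress and biomarker are not in the documents, so they are assumed and varied.

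**1. Pooled reading: type I error.** With no true association at either level, the variance of the pooled correlation is inflated by

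D = 1 + (k − 1) × ICC_stress × ICC_marker,

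and the actual type I error is 2 × P(Z > 1.96/√D). For example, with k = 5 and both ICCs 0.5, D = 1 + 4 × 0.25 = 2, 1.96/1.414 = 1.386, and the error is 16.6%. A simulation with 149 players and 5,000 runs agrees:

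| ICC in both | k = 3, D | k = 3, formula | k = 3, simulated | k = 5, D | k = 5, formula | k = 5, simulated |
|---|---|---|---|---|---|---|
| 0.3 | 1.18 | 7.1% | 7.2% | 1.36 | 9.3% | 9.1% |
| 0.5 | 1.50 | 11.0% | 11.3% | 2.00 | 16.6% | 16.3% |
| 0.7 | 1.98 | 16.4% | 16.9% | 2.96 | 25.5% | 24.8% |

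If one ICC is 0, D = 1 and there is no inflation (simulated 4.5% and 5.2%, with the other ICC at 0.6). The number of players does not matter. At ICC 0.5 in both, 134 and 200 players give 11.3% and 11.4% (k = 3), and 16.6% and 16.5% (k = 5).

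**2. Pooled reading: what is estimated.**

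r_pooled = r_between × √(ICC_stress × ICC_marker) + r_within × √((1 − ICC_stress)(1 − ICC_marker)).

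With both ICCs 0.5:
- r_within = 0.3 and r_between = −0.3 give 0.15 − 0.15 = 0, so real tracking is hidden.
- r_within = 0 and r_between = 0.4 give 0.20, a correlation without any tracking.
- r_within = 0.4 and r_between = 0 also give 0.20, so the coefficient cannot tell these last two cases apart.

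**3. Season period.** Assume one sample in each of three periods, with both variables shifted by −0.5, 0 and +0.5 SD and no other association. The period variance is (0.25 + 0 + 0.25)/3 = 0.167, so the pooled r is 0.167/1.167 = 0.14. With ±0.3 SD it is 0.06/1.06 = 0.06.

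Centring on the player alone, as a repeated-measures correlation does, makes this larger. At ICC 0.5, the sum of squares per player is 0.5 from period and (3 − 1) × 0.5 = 1.0 from residual variation, so r = 0.5/1.5 = 0.33. Centring on player and period together removes the shift, and simulated type I error is then 4.6–5.4%.

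**4. Per-timepoint or player-mean reading.** Each has one pair per player. Player means gave a simulated type I error of 4.5–5.5% with 149 players. A single timepoint meets the independence assumption by construction. Both describe differences between players only.

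**The case against.** The strongest reply is that the article does not say timepoints will be pooled. Correlations per timepoint or on player means are equally compatible with the text and hold 5% per test. The authors plainly know about repeated-measures dependence, and a condensed article may leave the unit of analysis to a fuller document. This stands against a stronger reading that a reader might infer, namely that the secondary aim will produce false positives. The documents do not support that. It requires pooling, which is allowed but not stated, and non-zero ICCs in both measures, for which no values are given.

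A reader might also infer that the plan estimates the wrong quantity. That goes too far as well. The first clause of the aim asks only for an association, and a between-player correlation is a legitimate answer to it.

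The period argument has limits too. Equal shifts in the same direction are an assumption, and common seasonal movement is itself a form of co-movement within players. Whether it should count is a choice the analysis has to make openly.

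What remains is more than missing detail. The method is named, and under none of its three readings does it isolate within-player change. The other listed analyses (Bland-Altman, ROC curves, repeated-measures ANOVA by season period) do not do so either, and the dependence sentence is tied to a model that cannot cover this question.

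**Conclusion.** The point holds in a limited form. The named method does not fit a design with three to five pairs per player, and it leaves the monitoring clause of the secondary aim unanswered on every reading.

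Inflated type I error and mixing of levels are conditional on pooling. The inflation then runs from none (either ICC 0) through 7.1–9.3% (both ICCs 0.3) to 16.4–25.5% (both 0.7), and these ICCs are assumptions. On the other two readings the tests are valid and the shortfall is one of scope.

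The within-player target rests on the monitoring wording of the aim and of Table 1, not on the association clause. The matter concerns a secondary aim. Nothing about the sample size follows from it, and the difference between 200 players in the abstract and 149 in the sample size section does not affect it.

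**What to change.** Replace the bivariate correlation with a linear mixed model for each biomarker:

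- outcome: the biomarker, log-transformed where appropriate;
- stress entered as two terms, the player's mean rating and his deviation from that mean;
- random intercept for player;
- season period as a fixed effect.

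Report the coefficient of the deviation as the answer to the monitoring question, and the coefficient of the player mean separately as the between-player association. State the unit of analysis (player-timepoint) and which coefficient answers which clause of the aim.

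An unadjusted repeated-measures correlation should not be offered as an equivalent. It handles the repeated pairs but leaves common period shifts in the coefficient and can enlarge their effect (0.33 against 0.14 in the example).

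The cost is a revised analysis paragraph and a little more analysis work, with no new data. The within-player coefficient, adjusted for period, will rest on only three to five samples per player, and its confidence interval should be reported with that in mind.
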